### 6.5. Methods

Under a regime of fasting from liquids and solids from midnight the previous evening, in the morning around 8.00 AM a blood sample will be taken from all patients. In Subgroup 1 and 3, the blood sample will be obtained only at baseline. In Subgroup 2, the blood sample will be obtained at baseline before the beginning of therapy and at 3-, 6-, 12-month intervals during systemic therapy. Sample storage will be performed at room temperature for 30 min, followed by centrifugation of the sample (3000× *g*; duration: 15 min) and subsequent separation to obtain a plasma sample. The plasma samples will be transported within 30 min to the chemistry laboratory in a suitable refrigerated container with ice at a temperature of 4 °C after centrifugation of the blood to remove the erythrocytes. As soon as they are delivered to the laboratory, the plasma samples appropriately labeled with the sample identification code will be stored at −80 °C until analysis.

For protein and metabolite corona experiments, in collaboration with the nanodelivery Lab of Sapienza of Rome, we developed a cross-reactive sensor array platform with cancer detection capacity made of three liposomal formulations with different surface charges, i.e., cationic 1,2-Dioleoyl-3-trimethylammonium propane (DOTAP), anionic 1,2-Dioleoyl-sn-glycerol-3-phosphoglycerol (DOPG), and a zwitterionic mixture made of dioleoylphosphatidylcholine (DOPC) and cholesterol [19]

For the proteomics–NP studies, proteins will be identified and quantified by nano-high-performance LC (nanoHPLC) coupled to MS/MS (nanoHPLC−MS/MS). The acquired raw MS/MS data files from Xcalibur software (version 2.2 SP1.48, Thermo Fisher Scientific, Washoe County, NV, USA) will be searched against the Swiss-Prot human database using the MaxQuant search engine with the automatic setting for tryptic peptide matching and label-free analysis. For each NP type, a list with all the identified proteins and their relative protein abundance (RPA, a quantitative estimation of their abundance within the protein corona) will be provided. The list of proteins will be utilized to discover new biomarkers associated with the PCa using sensor array technology [20].

Metabolites will instead be analyzed by an untargeted metabolomic approach. Before analysis, Quality Control (QC) samples will be prepared for further instrumental system conditioning and sample normalization over time. Data acquisition for samples, controls, and QCs will be obtained by ultra-high-performance liquid chromatography coupled with untargeted high-resolution mass spectrometry (UHPLC-HRMS). A data acquisition worklist will comprehend a QC run every 5 sample runs for subsequent QC-based normalization. At the end of the data acquisition worklist, a series of QCs will run in data-dependent acquisition tandem mass spectrometry (MS/MS) for subsequent tentative compound identification. All samples will be acquired in positive and negative ion mode for maximum compound coverage. After raw data collection, pre-processing analysis using Compound Discoverer software on samples, controls, and QCs will be needed to extract the *m*/*z* from the raw files, to align the variables (features) among all acquired runs, normalize each feature over time, and remove contaminants present in the blank sample. After data pre-processing, a data matrix will be obtained for further statistical analysis. Features that will be selected from statistical analysis as putative biomarkers will be then tentatively identified by matching the experimental MS/MS spectra to those present in databases, such as the Human Metabolome Database (HMDB), Lipid Maps, Kyoto Encyclopedia of Genes and Genomes (KEGG pathway) and Metabolika. Lipidomics will be carried out using a similar approach to metabolomics, but all instrumental parameters will be adjusted to lipids, including chromatography (C8 column, mobile phases, and gradient), MS tuning and parameters (*m*/*z* range and injection time), and pre-processing and identification tools (Figure 2).

### 6.6. Statistical Analysis

In the analytical field, we often work with complex problems in which the variables are numerous and sometimes uncontrollable; furthermore, information may be difficult to extract due to the presence of experimental noise, random or systematic correlations between variables, and useless or redundant variables. It is therefore essential, for a correct interpretation of the analytical data, to eliminate redundant and superfluous information to evaluate which are the most significant variables and consider any correlations between them.

For proteomics analysis, statistics and multivariate data processing will be carried out. A three-dimensional data matrix consisting of sample information, identified peptides, and the normalized ion intensity will be generated. The resultant three-dimensional matrix will be imported to SIMCA-P 14.1 software (Umetrics AB, Umeå, Sweden) for multivariate statistical analysis, including principal component analysis and orthogonal partial least squares discriminant analysis (OPLS-DA). The functional analysis of differentially expressed proteins will be performed using Gene Ontology (GO). The strength of this approach lies not only in pinpointing individual predictors (i.e., single biomarkers) but also in the pattern recognition enabled by a protein corona sensor array. The differentiation between the groups of samples may arise due to a “global change” involving several predictors that are systematically altered simultaneously, resulting in distinctive global protein patterns unique to the pathological conditions. By concentrating on unique patterns derived from a large number of subjects through a set of informative predictors, we will achieve more accurate predictions of PCa and different stratified mHSPCa patients than current methods allow.

For metabolites–coronas, a principal components analysis (PCA) and discriminant analysis (partial least squares discriminant analysis, PLS-DA) will, in general, be applied. For the purposes of the project, the first step will be the application of the unsupervised PCA technique, to understand the tendency of the samples to divide into different clusters depending on whether they belong to the group of healthy subjects or to the group of pathological subjects, and to highlight the possible presence of outliers (for example, very diluted samples). To further characterize differences between groups, supervised PLS-DA methods will be used. The application of PLS-DA could allow us to obtain a clear separation between different groups consistent with the characteristics of the pathology.

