
### 6.2. Study Design

We developed the design of an experimental prospective single-center study with patients allocated in a 1:1:1 ratio of one of the three arms. A longitudinal analysis will also be applied to a 12-month interval observation. The protocol has been approved by our Ethic Committee Sapienza Policlinico Umberto I, Prot 0919/2021. The protocol will start on January 2025.

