#### 6.3.2. Primary Endpoints

The first primary endpoint is the construction of predictive diagnostic models on serum from patients with a histological diagnosis of PCa versus patients with BPH using proteomics, metabolomics, and lipidomics of the biomolecular coronas that form between nanoparticles and serum.

A second endpoint is the construction of a predictive model for the response to treatment of patients with an initial diagnosis of mHSPC for the personalization of therapies and for the stratification of such patients considering individual characteristics such as genetics, lifestyle, and more, as foreseen by precision medicine, using metabolomics and lipidomics of the biomolecular coronas that form between nanoparticles and serum.

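### Section 6.6 names only group-discrimination methods, with none for the serial samples of Subgroup 2 or for the promised 12-month longitudinal analysis

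*Protocol article*

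**What the plan says.** All places are in the protocol article.

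- **Sampling (6.5).** "In Subgroup 2, the blood sample will be obtained at baseline before the beginning of therapy and at 3-, 6-, 12-month intervals during systemic therapy". By contrast, "In Subgroup 1 and 3, the blood sample will be obtained only at baseline". Repeated measures therefore arise in Subgroup 2 only.
- **Design (6.2).** "A longitudinal analysis will also be applied to a 12-month interval observation". No technique is attached to this sentence.
- **Endpoint (6.3.2).** "A second endpoint is the construction of a predictive model for the response to treatment of patients with an initial diagnosis of mHSPC". It is listed under the primary endpoints and is to be built "using metabolomics and lipidomics of the biomolecular coronas that form between nanoparticles and serum"; proteomics is not in that list.
- **Methods (6.6).** For metabolite coronas, "a principal components analysis (PCA) and discriminant analysis (partial least squares discriminant analysis, PLS-DA) will, in general, be applied". For proteomics, PCA and OPLS-DA are named, and the same paragraph expects better prediction of stratified mHSPC patients. The text describes how samples separate into groups. It does not mention repeated samples, pairing, or how samples from one man are handled.

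**The concern.** The design has a cross-sectional half (cancer versus BPH, one sample per man) and a longitudinal half (mHSPC on therapy, up to four samples per man). The named techniques fit the first half. PCA, PLS-DA and OPLS-DA in standard form take one row per sample and have no term for the man or the visit.

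Two things are at stake if they are carried over to the serial samples.

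1. **Change on therapy.** Comparing baseline with follow-up as two separate groups leaves stable differences between men in the error, so real within-man change is harder to see.
2. **Prediction of response.** If all visits enter as rows under one responder label and validation splits by sample, samples of the same man can sit in both training and test sets. The model can then score well by recognising men, which would look like success on a primary endpoint.

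The first follows wherever ordinary PLS-DA compares visits. The second needs two further steps that the article does not describe.

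**Working it through.** **Inputs.** From the article: four planned samples per man in Subgroup 2. The article gives no group size, effect size, alpha or within-man correlation, so there is no stated figure to reproduce. Everything else below is assumed.

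**1. Within-man change, one feature, baseline versus one follow-up.** Assume n = 30 men, a change of 0.5 SD (SD at one visit), correlation rho between visits, two-sided 5%.

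- Paired: SD of change = sqrt(2(1 − rho)). At rho 0.5 this is 1.0, so the noncentrality is 0.5 × sqrt(30) = 2.74 on 29 degrees of freedom. Power is 75%.
- Pairing ignored: standard error sqrt(2/30) = 0.258, so the statistic centres on 0.5/0.258 = 1.94 against a critical value of 2.00 (58 degrees of freedom). Because the visits are correlated, its true SD is sqrt(1 − rho) = 0.71. Power ≈ Φ((1.94 − 2.00)/0.71) ≈ 46%; simulation gives 47%. The true size of this test is about 0.5%, not 5%.

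| rho | pairing ignored | paired |
|---|---|---|
| 0.3 | 47% | 61% |
| 0.5 | about 47% | 75% |
| 0.7 | about 46% | 93% |

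**2. One feature against a man-level response label, four visits pooled as if independent.** Design effect = 1 + (4 − 1) × ICC. At ICC 0.5 it is 2.5. The true error of a nominal 5% test is 2 × (1 − Φ(1.96/sqrt(2.5))) = 21.5%. At ICC 0.05, 0.3 and 0.7 it is 6.8%, 15.5% and 26.6%.

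**3. PLS-DA with no true signal.** Assumptions: 300 features, 2 components, four rows per man, response label unrelated to the features, 7-fold cross-validation, 80 runs per setting. In the factor settings, 23% of each feature's variance is uncorrelated noise. The true AUC is 0.50. Mean cross-validated AUC at ICC 0.5 with folds split by sample:

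| Feature structure | 30 men | 60 men |
|---|---|---|
| Mutually independent | 0.99 | 0.96 |
| 20 latent factors | 0.70 | about 0.64 |
| 10 latent factors | about 0.63 | 0.58 |
| 5 latent factors | 0.58 | 0.55 |

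At ICC 0.05 the inflation is small: about 0.57 to 0.63 with independent features for 20 to 60 men, and about 0.51 with latent factors. Keeping all samples of a man in one fold gives about 0.5 in the settings checked. In a companion null simulation (200 independent features; 20, 40 or 80 men), using only the baseline sample gave 0.48 to 0.53.

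The direction of the bias is therefore stable, but its size depends strongly on the ICC, the number of men and how correlated the features are.

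**The case against.** The strongest reply is that the article describes no faulty analysis. Several parts of it stand.

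- **Pooling is not stated.** A reader might infer that every sample will be treated as an independent subject in the response model. The article does not say this. It neither pools visits nor describes cross-validation, and a baseline-only model, or one model per visit, is an equally natural reading with one row per man.
- **No method is expressly assigned to the response model.** The metabolite paragraph speaks of healthy versus pathological subjects, which is the diagnostic question. OPLS-DA belongs to proteomics, which the response endpoint does not list.
- **The lists are open.** The wording is qualified, and section 6.2 presents the longitudinal analysis as an addition.
- **The data matrix proves nothing.** A reader might infer from "A three-dimensional data matrix consisting of sample information, identified peptides, and the normalized ion intensity will be generated" that patient and visit are lost. Sample information is undefined and can hold both, and the sentence concerns proteomics only.
- **Near-perfect false AUCs need independent features.** Omics features are usually correlated, and with latent factors the inflation is much smaller.
- **Detail may be elsewhere.** Fold structure and model specification are commonly left to a full protocol or analysis plan that is not shown.

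What the reply does not remove is the mismatch. The article does choose its techniques, and those chosen suit only the cross-sectional comparison, while it commits to serial sampling and a longitudinal analysis.

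**Conclusion.** The point holds in a conditional form. The named techniques do not match the repeated sampling that the article commits to in Subgroup 2. Used on the serial samples, they discard the pairing. Under the assumed 30 men, 0.5 SD change and rho 0.5, that takes power from 75% to about 47%.

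If visits were also pooled under one response label and validated by sample, apparent prediction would rise above the true AUC of 0.50: roughly 0.60 to 0.99 at ICC 0.5, from 10 latent factors up to independent features, and close to 0.50 when the ICC or the number of factors is low. This is a risk left open by the text, not a planned analysis, and a response model on baseline samples alone does not carry it.

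It should be corrected because the response model is a primary endpoint and the remedy is cheap. The size of the harm cannot be fixed from the article, which gives neither a group size nor a within-man correlation.

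**What to change.** In section 6.6, add a paragraph for Subgroup 2.

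1. **Response model.** State which samples enter. Fit one row per man: the baseline sample, or baseline plus change to a fixed visit as extra columns. If several visits enter as rows, keep all samples of a man in the same validation fold and permute response labels by man.
2. **Twelve-month longitudinal analysis.** In place of ordinary PLS-DA, name a within-man method: multilevel PLS-DA on data centred within each man, or ANOVA-simultaneous component analysis with patient and visit factors. Support it with per-feature mixed models with a random patient effect and a visit term.

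No new patients, samples or assays are needed. The costs are a little more analysis work, possibly software beyond SIMCA, and lower apparent accuracy than sample-level fitting would show.

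### Both primary endpoints are the building of a model with no performance measure, so a classifier with no predictive value would meet them, and separation in the fitted samples would not expose it

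*Protocol article*

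**What the plan says.** Section 6.3.2 of the protocol article gives two primary endpoints.

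- Endpoint 1 (PCa versus BPH): "The first primary endpoint is the construction of predictive diagnostic models on serum".
- Endpoint 2 (mHSPC): "A second endpoint is the construction of a predictive model for the response to treatment of patients".

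Neither names a sensitivity, specificity, AUC or error rate, a target value, or a method to compare against.

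Section 6.6 names the tools. Proteomics gets principal component analysis and OPLS-DA. Metabolite data get an unsupervised principal component analysis first, to look at clustering and outliers, and then a supervised step: "To further characterize differences between groups, supervised PLS-DA methods will be used". The result hoped for from that step is that "The application of PLS-DA could allow us to obtain a clear separation between different groups consistent with the characteristics of the pathology".

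The proteomics paragraph of the same section also predicts that the corona pattern will give more accurate prediction, for PCa and for stratified mHSPC, than existing methods. It does not name those methods or say how accuracy will be measured.

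**The concern.** A primary endpoint should be able to come out either way. Building a model is an activity, and it is complete once the software has run. A classifier that performs like a coin toss on new patients has still been constructed.

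The one classifier result described does not fill the gap. PLS-DA and OPLS-DA choose their directions using the class labels. When features are numerous relative to patients, the score plot separates the groups whether or not the labels carry any biology. A reader who takes the endpoint and the described result at face value could report success on noise.

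At stake are the claims attached to the models: telling cancer from benign disease, predicting response to systemic treatment, and doing so better than current practice. None is tested by the endpoints as written.

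**Working it through.** **No figure to reproduce.** The article gives no group size, power or accuracy target. The check is therefore what the described analysis returns when there is nothing to find.

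**Inputs**
- Features: Section 5.1 reports 178, 256 and 179 proteins for the three liposomes in the earlier sensor-array study. One liposome gives p = 178 at the low end. Stacking all three gives 178 + 256 + 179 = 613 columns. For untargeted metabolomics or lipidomics, p = 2000 and 3000 are assumed.
- Men per group: 20, 50 and 100, assumed.
- Two equal groups, consistent with the 1:1:1 ratio in Section 6.2.

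**Step 1, by formula.** Take N men in total, p independent standardised noise features and labels y = ±1. The first PLS component scores the men by XX′y. Each man's own data contribute about p·y to his score. The other men contribute noise with variance about pN. The group means thus lie 2p apart with standard deviation √(pN) in each group, so

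apparent AUC ≈ Φ(2p / √(2pN)) = Φ(√(2p/N)).

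- p = 178, N = 40: Φ(√8.90) = Φ(2.98) = 0.999
- p = 178, N = 100: Φ(√3.56) = Φ(1.89) = 0.970
- p = 178, N = 200: Φ(√1.78) = Φ(1.33) = 0.909
- p = 613, N = 200: Φ(√6.13) = Φ(2.48) = 0.993

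This is for one component. A second component raises every value.

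**Step 2, by simulation.** Pure noise, autoscaled two-component PLS-DA, class cut-off 0.5, 60 data sets per row. The fit on the training samples is compared with 7-fold cross-validation (folds balanced by group, model refitted in each fold) and with fresh noise samples.

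| Men per group | p | Apparent accuracy | Apparent AUC | Perfect separation | Cross-validated AUC | New-sample AUC |
|---|---|---|---|---|---|---|
| 20 | 178 | 1.000 | 1.000 | 100% | 0.515 | 0.524 |
| 20 | 613 | 1.000 | 1.000 | 100% | 0.488 | 0.505 |
| 20 | 2000 | 1.000 | 1.000 | 100% | 0.502 | 0.508 |
| 50 | 178 | 0.991 | 0.999 | 42% | 0.530 | 0.503 |
| 50 | 613 | 1.000 | 1.000 | 100% | 0.507 | 0.487 |
| 50 | 2000 | 1.000 | 1.000 | 100% | 0.499 | 0.484 |
| 100 | 178 | 0.905 | 0.967 | 0% | 0.493 | 0.484 |
| 100 | 613 | 1.000 | 1.000 | 98% | 0.503 | 0.503 |
| 100 | 2000 | 1.000 | 1.000 | 100% | 0.486 | 0.506 |

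Repeat runs with p = 3000 gave an apparent AUC of 1.00 at every group size. Across all runs the mean cross-validated AUC lay between 0.38 and 0.53. Values well below 0.5 arise when folds are not balanced by group, a known artefact on null data, and they are not a sign of signal.

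**Step 3, OPLS-DA.** For a two-class outcome OPLS-DA rotates the same PLS fit, so these results carry over to the proteomics analysis.

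**The case against.** The strongest reply is that this is a condensed article. Cross-validation, permutation tests and choice of components commonly sit in a full protocol or SAP, and their absence here is no fault. That is right. If such a document validates the classifier, the danger of reading a fitted score plot as evidence largely goes away. It would not repair Section 6.3.2: a model with a cross-validated AUC of 0.5 would still satisfy an endpoint defined as construction.

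It can also be said that Section 6.3.1 shows the real purpose, which is effective discrimination and better diagnostic accuracy. That is the aim, but the endpoint does not measure it.

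A reader might infer more than the text supports:

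- **That separation is the formal success rule, so the trial cannot return a negative answer.** The sentence in Section 6.6 is worded as a possibility and concerns metabolites. For proteomics OPLS-DA is named, but separation is not made the evidence.
- **That features are selected on the full data before validation.** The phrase "eliminate redundant and superfluous information to evaluate which are the most significant variables" comes from a general opening paragraph and fixes no step or data set. In Section 6.5, "Features that will be selected from statistical analysis as putative biomarkers will be then tentatively identified" describes chemical annotation after the analysis.
- **That the best of nine models (three liposomes by three omics) will be picked.** No such choice is planned. The liposomes are described as one sensor array, and endpoint 2 omits proteomics.
- **That noise always separates perfectly.** It does not with 178 features and 100 men per group, although the apparent AUC is still 0.967.

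**Conclusion.** The point stands and should be settled before the data are analysed. As written, both primary endpoints are met by any fitted model, and this follows from the endpoint wording alone, without any assumption.

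The simulation adds that the one classifier result described offers no protection: an apparent AUC of 0.97 to 1.00 on noise against cross-validated values around chance. That part rests on assumed group sizes of 20 to 100, on independent features, and on assumed feature counts above 613. Correlated features would act like a smaller p, and larger groups would lower the apparent AUC, in line with Φ(√(2p/N)). The promise of better accuracy than current methods cannot be judged until a measure and a comparator are named.

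**What to change.** - **Endpoint 1:** the out-of-sample AUC (or sensitivity and specificity), with 95% CI, of one pre-named model for PCa versus BPH.
- **Endpoint 2:** the out-of-sample performance, with 95% CI, of the mHSPC response model.
- **Success rule:** for each endpoint, a value fixed in advance that the lower confidence bound must exceed. If better accuracy than current methods is to be claimed, name the comparator and assess it in the same patients.
- **Estimation:** cross-validation with scaling, any feature selection and the choice of components redone inside each training fold. Balance folds by group, and keep all samples from one man in the same fold, since Subgroup 2 is sampled repeatedly. Add a label-permutation test of the whole procedure.
- **Reporting:** label score plots and any model fitted to all samples as descriptive.

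Combining liposomes and omics into one row per patient is one way to arrive at a single pre-named model, but it is optional.

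The cost is protocol wording and computing time, with no additional patients or assays. The reported accuracy will be less favourable than the apparent figures.
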